### Participant inclusion criteria

The study is conducted with youth with cancer and one caregiver (primary caregiver). *Inclusion criteria for youth with cancer*: a new diagnosis of any type of cancer (within 4 weeks of diagnosis), between the ages of 10 and 17 years, medically suitable for participation (determined by the patient’s oncologist) and in active treatment (i.e., not palliative). Youth were excluded only if the treating clinical team thought a psychiatric or developmental disorder prevented them from active participation (e.g., completing assessment measures). *Inclusion criteria for caregiver*: primary caregiver of youth with cancer (as outlined above). Both youth with cancer and caregiver must agree to participate in the study. Given the culturally diverse population at HSC, families with limited English fluency but interested in participating are provided with translation services.

### Participant exclusion criteria

*Exclusion criteria for youth with cancer*: a diagnosed psychiatric, physical, or developmental disorder which prevents him/her from completing assessment measures; is considered not medically suitable for participation (as determined by the treating oncologist); primary caregiver does not participate. *Exclusion criteria for caregiver*: does not self-identify as the primary caregiver; youth with cancer does not participate.

### Recruitment procedure

Potential participants are identified by the treatment team and central database. Those who meet the eligibility criteria receive a brief synopsis of the study by a health care professional that is known to them. If they are then interested in hearing more about the study, a trained research assistant meets with them to review the study in more detail, verbally guides them through the written consent form, and provides some time for the participant to review it independently. If patient and caregiver decide to participate they sign the written consent form in the presence of the research assistant. Patient and caregiver are consented separately. Participation is voluntary and dyads are informed that they may withdraw at any time. After the consent form is signed, the baseline measures are completed and the family is randomized. A similar assessment battery is completed 12 months later. Each participant (patient and caregiver in each family) receives a $25 gift card at baseline and completion of study as an expression of gratitude for their participation.

### Sample size

As recommended for pilot RCT [33], enrolling 36–40 consenting patients-caregiver dyads, 18–20 in each group, will be acceptable to achieve the study objectives (see Fig. 2, participant flow chart).

### Intervention

#### CG

This group receives available psychosocial care services at the institution; these services (e.g., child life, psychology, art and music therapy, and psychiatry) are accessible to both CG and IG groups based on the clinical judgement of the core team. The core team consists of an oncologist, a social worker, and a nurse.

#### IG

The IG receives whatever available services the treating team recommends, as described above, and the EPSI services on a monthly basis for 1 year. EPSI consists of the following components: (1) translating screening for *psychosocial risk, distress, and mental health* assessments results at baseline into intervention recommendations, mapped to resources based on levels of psychosocial risk (PAT: universal, targeted, clinical) and levels of depression and anxiety (mild, moderate, and high), as determined by the standardized norms for the measures completed shortly after diagnosis; (2) monthly distress screening also classified as mild, moderate, and high for mapping resources and recommendations; (3) these screening results and resource recommendations are provided to *the treating team and the family* and resources are available in the treatment center, online, and/or in their local community; (4) information on risk, distress, and mental health results are highlighted using color to convey severity of identified risk and mental health concerns (green = low risk, yellow = medium, red = high risk); finally (5) a key component of EPSI is the utilization of a health professional trained in psychosocial assessment and intervention in pediatric oncology called *the Psychosocial Navigator (PSN).* The term ‘navigator’ is used in other health care contexts where the role typically consists of assisting families to navigate the health system [34]. In the IG, the PSN serves as the contact person for families and the treating team, as the PSN provides feedback after the initial screening and monthly psychosocial distress screening follow-up for 12 months. Examples of resource recommendations by screening level are presented in Table 1. A copy of the Communication Summary Profile (CSP) with specific psychosocial service recommendations is presented in Fig. 3. An example of the monthly assessments and recommended resources that are communicated to the youth, caregiver, and treating team is presented in Fig. 4. EPSI intervention addresses several of the barriers previously identified by psychosocial health care providers (HCPs), including *how* to integrate screening results, limited knowledge of validated measures, and using the PSN we address the concern of the limited clinical resources that are available for conducting screening and ongoing monitoring of psychosocial needs [22].

**Table 1 Tab1:** Examples of resource recommendations by risk level

Child/adolescent	Resources
*Universal/low*	Hospital volunteers
	Child life
	Look good feel better program
	Interlink nurses
	Hospital game room
	Borrowing distraction resources (e.g., games, audiobooks) from hospital resource center or local library
*Targeted/moderate*	Social work
	Web-based resources (https://youth.anxietycanada.com/, MindShift app)
	Mindfulness resources (in hospital or online; https://www.uclahealth.org/marc/mindful-meditations)
	Art, music, animal therapy
	Wellspring Cancer Support Center (https://wellspring.ca/)
	Camp Ooch in the city
	Upopolis (https://www.upopolis.com/login.html)
	Psychology consult
	(See universal/low resources)
*Clinical/high*	Psychology
	Psychiatry
	(See universal/low and targeted/clinical resources)
**Parent/caregiver:**	
Universal/low	Canadian Cancer Society web-based resources (http://www.cancer.ca/en/cancer-information/cancer-type/childhood-cancer-information/your-child-has-cancer/?region=on)
	POGO ( https://www.pogo.ca/programs-support/resource-guide/)
	SickKids resources guide for families facing childhood cancer ( https://www.sickkids.ca/PDFs/Haematology-Oncology/66601-oncology%20resource%20guide.pdf)
	Ontario Parents Advocating for Children with Cancer Parent Liaison
Targeted/moderate	Social work/resource navigators
	Mindfulness resources (in hospital or online; https://www.uclahealth.org/marc/mindful-meditations)
	Wheels of Hope
	Web-based resources (https://www.anxietycanada.com/adults/introduction ; MindShift app)
	Spiritual services (in hospital or community)
Clinical/high	Psychology
	Consult with general practitioner
	(See universal/low and targeted/clinical resources)

**Fig. 3 Fig3:**
[figure not shown]
Example of Baseline Communication Summary Profile for a Fictional Patient

**Fig. 4 Fig4:**
[figure not shown]
Example of Monthly Distress Thermometer Communication for a Fictional Patient

All participants complete the assessment measures at baseline and 12 months and participants in the IG group also complete the screening measure monthly (see below). At the 12-month follow-up, based on their preference, participants will either have survey packets mailed to them with pre-stamped envelopes to return completed surveys, or emailed to them via a secured link to REDCap. In the IG, personalized results from the psychosocial risk assessment and anxiety and depression assessment at baseline, and monthly distress screenings, are used to tailor resource recommendations for the youth and caregiver, which are shared with them and the youth’s treating team. The validated instruments are described below. Additionally, at 12 months, after completing the quantitative measures, the IG group participants complete a brief questionnaire of intervention acceptability and are invited to engage in a short semi-structured interview (approximately 15 min; see Table 3) where they are asked to describe their overall experience of the study. This interview is conducted either in person or over the telephone, depending on participant preference and availability. Interview data are audio-recorded and transcribed verbatim. The time line for the IG and CG is presented in Fig. 2.

### Assessments and outcome measures

The primary outcomes are feasibility and acceptability of the intervention. Secondary outcomes are measures of anxiety and depression symptoms and quality of life outcomes in the youth and caregiver, separately. Exploratory outcomes are measures of coping, social relationships, and physical functioning (pain, fatigue, and sleep quality). Demographic and clinical variables are also collected (see Table 2).

**Table 2 Tab2:** Measures for both intervention and control group arms

Questionnaire	Measures	Caregiver self-report		Child/teen self-report		Parent-proxy report	
		Baseline	12-month F/U	Baseline	12-month F/U	Baseline	12-month F/U
^a^PAT	Psychosocial risk	X	X				
^a^PROMIS-anxiety	Anxiety	X	X	X	X		
^b^(PI-ED)	Anxiety and depression			X	X		
^a^PROMIS-Depression	Depression	X	X	X	X		
^b^PedsQL-generic	Quality of life (QOL) of child/teen			X	X	X	X
^b^PedsQL-cancer	QOL of child/teen (related to cancer)			X	X	X	X
^a^DT (intervention dyads also complete DT on a monthly basis)	Distress	X	X	X	X		
^b^PROMIS-fatigue	Fatigue	X	X	X	X		
^b^PROMIS-Emotional Support	Emotional support	X	X	X	X		
^b^PROMIS-Peer Relationships	Peer relationship support			X	X		
^b^Pittsburg Sleep Quality Index	Sleep quality	**X**	**X**	**X**	**X**		
^b^Response to Stress Questionnaire (RSQ-PC)	Coping with cancer diagnosis	X	X	X	X		
^b^Impact of Events Scale (IES-R)	Post-traumatic stress	X	X	X	X		
^b^Financial impact	Financial impact of diagnosis and treatment	X	X				
^c^Satisfaction questionnaire (intervention dyads only)	Satisfaction with intervention and study experience overall		X		X		

^a^Used for screening

^b^Used for exploratory purposes

^c^Used for acceptability

### Feasibility and acceptability

Outcomes and endpoints for feasibility are measured by criteria of intervention acceptability; recruitment and retention; intervention satisfaction; and feasibility of completing outcome measures of intervention effectiveness.

Acceptability will be assessed using (a) estimates of recruitment, retention, and withdrawal rate; (b) estimates of completed assessment screenings, data collection procedures, and specific outcome measures; (c) in the intervention group, youth’ and parents’ perceptions of the acceptability of EPSI intervention, including their acceptability of monthly screening and feedback by the PSN, as well as their views about the intervention gathered during the end of intervention interview. Finally, (d) examination of treatment effects (e.g., effect sizes, variance measures/standard deviation) on secondary mental health and quality of life outcomes and exploratory variables will inform the selection of outcome measures for the future, definitive RCT.

*Intervention acceptability* is measured by participation in screening, assessment, and intervention activities (defined as treatment accepters when the participant completes all required measures and questionnaires). Recruitment and *retention* will be measured by (i) accrual and dropout rates; and (ii) proportion of completed questionnaires (defined as 100% when all measures completed at baseline and 12 months post-baseline). *Intervention satisfaction* will be measured by (i) comparing recruitment and retention between both groups; (ii) brief questionnaire completed by all caregivers and youth at the completion of study; and (iii) by the semi-structured interview completed by youth and caregivers who participate in the IG (Table 3). Finally, potential benefits of EPSI will be estimated comparing the secondary outcomes (mental health and quality of life) and exploratory outcomes (coping, social relationships, and physical functioning) in the IG and CG.

**Table 3 Tab3:** Semi-structured interview questions

1. **Thinking back to when you first agreed to participate in the study, what was it about the project that made you say “yes”?**	
2. **What was it like for you to participate in the study? (Tell us about your own experience?)**	
3. **What were your expectations about being in this study?**	
4. **How were your expectations met or not met? (Explain.)**	
5. **How did you find the experience with the Psychosocial Navigator?**	
6. **Do you have any additional comments or suggestions regarding the study?**	

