## Methods/design

### Study design

We use a parallel, randomized controlled pilot trial design with two study arms: the enhanced psychosocial intervention group (IG) and the treatment as usual control group (CG). Outcome assessments are conducted at baseline (2–6 weeks from diagnosis) and 12 months later (see Fig. 2 for timeline). Prior to the initiation of this study, we consulted with key stakeholders (community parents of children with cancer organization, oncologists, nurses, social workers, psychiatrists) regarding study design. We plan to continue to share outcomes of the study with stakeholders in order to foster continued engagement in psychosocial screening as a process.

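### Comparing recruitment and retention between arms cannot measure satisfaction with EPSI; satisfaction should rest on the intervention group's own reports

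*Protocol article*

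**What the plan says.** The Feasibility and acceptability section of the protocol article gives three measures of intervention satisfaction:

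- (i) "comparing recruitment and retention between both groups";
- (ii) a "brief questionnaire completed by all caregivers and youth at the completion of study";
- (iii) satisfaction judged "by the semi-structured interview completed by youth and caregivers who participate in the IG".

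The same section measures recruitment and retention in two ways. One is accrual and dropout rates, with no stated time point or recording rule. The other is the proportion of completed questionnaires, tied to baseline and 12 months.

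Study contact differs by arm. The paragraph after Fig. 4 in the Intervention section says "All participants complete the assessment measures at baseline and 12 months", and adds that "participants in the IG group also complete the screening measure monthly". The IG section says that "the PSN provides feedback after the initial screening and monthly psychosocial distress screening follow-up for 12 months". No scheduled study contact is described for controls between baseline and month 12.

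The Randomization and Recruitment procedure sections place consent and baseline measures before allocation.

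**The concern.** Item (i) is a stated measurement rule, not a detail left for later. It treats a difference between arms in joining or staying as a sign of how families feel about EPSI. Two features of the design break that link: recruitment is complete before anyone has an arm, and the arms differ in how often the study is in touch with families after baseline. Controls also have no experience of EPSI to be satisfied or dissatisfied with.

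The article says that the pilot will inform a definitive trial. The risk is that a chance gap in retention, or one related to contact, is carried forward as evidence that families liked or disliked the intervention.

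**Working it through.** **Recruitment.** The order is consent, baseline measures, then 1:1 allocation. At recruitment no family knows its arm, so numbers recruited per arm reflect the allocation process alone. This half of item (i) carries no information on satisfaction.

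**Retention: contact by arm.** Counting monthly contact for a year as 12 occasions, the intervention arm has 12 scheduled study contacts after baseline and the control arm has 1. Set against the two retention measures:

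| Retention measure | Same time points in both arms? | What else can move it |
|---|---|---|
| Dropout or withdrawal rate | Not stated | Occasions to decline, burden, holding effect of contact |
| Questionnaires completed at baseline and 12 months | Yes | Burden, holding effect of contact |

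Unequal opportunity to record a loss can therefore affect only the first row. In both rows, a difference mixes satisfaction with the effect of being contacted often.

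**How large could a recording effect be?** The documents give no monthly rate, so this is illustration only. Assume that a share h of families wishes to stop each month, that every such wish is recorded as a permanent loss in the intervention arm, and that 25–50% of such control families are willing again by month 12. Intervention loss is 1 − (1 − h)^12. Control loss is that figure times 0.75 to 0.50.

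| h | Intervention | Control | Gap (points) |
|---|---|---|---|
| 1% | 11.4% | 5.7–8.5% | 3–6 |
| 2% | 21.5% | 10.8–16.1% | 5–11 |
| 3% | 30.6% | 15.3–22.9% | 8–15 |

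The gap comes entirely from assuming unequal recovery. If both arms recover equally, it is zero. Monthly contact could also reverse the sign by keeping intervention families engaged.

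**Precision.** Trial status reports 38 dyads enrolled, which is 38/2 = 19 per arm under 1:1 allocation. At an assumed 80% retention in both arms:

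- half-width of the 95% interval = 1.96 × √(2 × 0.8 × 0.2 / 19) = 0.254, about 25 points;
- with 20 per arm and 70% retention: 1.96 × √(2 × 0.7 × 0.3 / 20) = 0.284, about 28 points;
- with 20 per arm, power to detect 70% against 90% retention is about 35% by the normal approximation and 24% by Fisher's exact test (two-sided 5% level, assumed).

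The planned sample size (36–40 dyads, 18–20 per group) rests on a pilot-trial recommendation with no power inputs, so there is no plan figure to reproduce beyond 2 × 18 = 36 and 2 × 20 = 40.

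**The case against.** The strongest reply is that nothing decisive hangs on item (i). It is one of three measures, and the other two are direct. In the quantitative analysis section, acceptability is judged by whether at least 75% of the intervention group give a favourable rating. The 70% retention and 30% withdrawal criteria apply to the sample as a whole. A spurious gap between arms could change none of these. This stands, and it is why the point is minor.

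A second reply is that monthly contact is the intervention, so leaving because it is burdensome, or staying because it helps, is informative. This stands in part. Such behaviour bears on feasibility and acceptability and should be reported. It still does not separate satisfaction from burden or from the pull of regular contact, and the control arm is no comparator for satisfaction with something it does not receive.

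A third reply is that imprecision is expected in a pilot. That is fair. The article acknowledges the small sample and plans frequencies and percentages for retention. The width is a further reason not to read the contrast as satisfaction; it is not a fault in the sample size.

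A reader might go further and infer that dropout is recorded on different schedules by design, so that any retention gap is an artefact. The documents do not support that. No rule for recording dropout is stated, and questionnaire completion uses common time points. A 12-month assessment of all participants is already planned. The gaps tabulated above rest on assumed rates found nowhere in the article.

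**Conclusion.** The point holds, as a minor one. Item (i) cannot measure what it names. Its recruitment half is uninformative because allocation comes later. Its retention half can be moved by contact intensity in either direction, and at about 19 dyads per arm a difference would be known only to within about ±25 points, assuming 80% retention.

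The recording concern is confined to the dropout or withdrawal rate. The feasibility and acceptability thresholds are unaffected. The documents do not establish the direction or size of any bias, so a retention gap can be said only to be possibly confounded with contact.

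**What to change.** In Feasibility and acceptability:

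1. Delete item (i) as a measure of intervention satisfaction. Rest satisfaction on the questionnaire and interview in the intervention group.
2. Reconcile who completes the questionnaire. This section gives it to all caregivers and youth, while Table 2 and the paragraph after Fig. 4 limit it to intervention dyads. Ratings of EPSI can come only from those who received it.
3. Report retention by arm descriptively, as feasibility only, defined in both arms by completion of the 12-month assessment. That assessment is already planned for everyone.
4. In the intervention arm, tabulate stopping monthly screening separately from leaving the study.

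The cost is a change of wording and one extra table, with no new data on outcomes. One weak indicator of satisfaction is lost.

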### Data collection

#### All participants (IG and CG)

At baseline (2–4 weeks post-diagnosis), all measures are completed in person with the assistance of a research assistant and in a few cases, interpreter services (see Table 2). At follow-up (12 months post-baseline assessment), all measures are available to participant dyads to complete during clinic appointments days, at home with prepaid postage to return the surveys, orally via phone, or by email via a secured link to REDCap. Survey measures require approximately 30–45 min to complete (see Table 2).

#### Psychosocial risk

*Psychosocial risk* is measured using the Psychosocial Assessment Tool (PAT) revised for a Canadian sample [24]. The PAT consists of 7 psychosocial domains: family structure and resources; social support; child problems; sibling problems; caregiver stress reactions; family problems; and family beliefs. Scoring of the PAT items generates a 3-tiered psychosocial risk system derived from PPHM [16, 17]: *universal:* the family reports many supportive resources and relatively low psychosocial risk (typical of most families); *targeted:* the family reports some supportive resources but also some psychosocial risk factors, which may impact illness adjustment or treatment adherence (smaller group of families); and *clinical*: the family reports few supportive resources and multiple areas of difficulty (e.g., mental health in the family, financial problems, and social isolation) that may impede illness adjustment or treatment adherence (this is an even smaller group of families). Scores < 1 indicate universal risk, 1–1.9 represent targeted risk, and > 2 represent clinical risk. This measure is administered at baseline and 12 months only.

#### Mental health measures

*Anxiety symptoms* are measured using the Patient-Reported Outcomes Measurement Information System (PROMIS) [35]. The PROMIS-anxiety is an 8-item (pediatric) and 6-item (adult) measure with a 5-point Likert scale from 1 (never) to 5 (almost never). The items are added to provide a raw score which is then converted to a T-score. For the purpose of this study, a T score below 55 represent low symptoms, 55–64.9 represent moderate symptoms, and ≥ 65 represent high symptoms. This measure is administered at baseline and 12 months only.

*Depression symptoms* are measured using the Patient-Reported Outcomes Measurement Information System (PROMIS) [35]. The PROMIS-depression is a 6-item (pediatric) and 8-item (adult) measure with a 5-point Likert scale from 1 (never) to 5 (almost never). The items are added to provide a raw score which is then converted to a T-score. For the purpose of this study, a T score below 55 represent low symptoms, 55–64.9 represent moderate symptoms, and ≥ 65 represent high symptoms. This measure is administered at baseline and 12 months only.

